# Implementing a nurse-enabled, integrated, shared-care model involving specialists and general practitioners in breast cancer post-treatment follow-up: a study protocol for a phase II randomised controlled trial (the EMINENT trial)

**DOI:** 10.1186/s13063-020-04740-1

**Published:** 2020-10-15

**Keywords:** Early breast cancer, Oncology, Shared-care, Quality of life, Protocol, Randomised controlled trial

## Abstract

**Background:**

Due to advances in early detection and cancer treatment, 5-year relative survival rates for early breast cancer surpass 90% in developed nations. There is increasing focus on promotion of wellness in survivorship and active approaches to reducing morbidity related to treatment; however, current models of follow-up care are heavily reliant on hospital-based specialist-led care. This study aims to test the feasibility of the EMINENT intervention for implementing an integrated, shared-care model involving both cancer centre specialists and community-based general practitioners for early breast cancer post-treatment follow-up.

**Methods:**

We describe a protocol for a phase II, randomised controlled trial with two parallel arms and 1:1 allocation. A total of 60 patients with early-stage breast cancer will be randomised to usual, specialist-led, follow-up care (as determined by the treating surgeons, medical oncologists, and radiation oncologists) or shared follow-up care intervention (i.e. EMINENT). EMINENT is a nurse-enabled, pre-specified shared-care pathway with follow-up responsibilities divided between cancer centre specialists (i.e. surgeons and oncologists) and general practitioners. The primary outcome is health-related quality of life as measured by the Functional Assessment of Cancer Therapy—Breast Cancer. Secondary outcomes include patient experience, acceptance, and satisfaction of care; dietary, physical activity, and sedentary behaviours; financial toxicity; adherence; health resource utilisation; and adverse events.

**Discussion:**

The trial is designed to identify the barriers to implementing a shared-care model for breast cancer survivors following treatment. Results of this study will inform a definitive trial testing the effects of shared-care model on health-related quality of life of breast cancer survivors, as well as its ability to alleviate the growing demands on the healthcare system.

**Trial registration:**

Australia and New Zealand Clinical Trials Registry ACTRN12619001594112. Registered on 19 November 2019

## Administrative information

The order of the items has been modified to group similar items (see http://www.equator-network.org/reporting-guidelines/spirit-2013-statement-defining-standard-protocol-items-for-clinical-trials/).

**Table Taba:** 

Title {1}	Implementing a nurse-enabled, integrated, shared-care model involving specialists and general practitioners in breast cancer post-treatment follow-up: a study protocol for a Phase II randomised controlled trial (The EMINENT Trial)
Trial registration {2a and 2b}.	Registry Name: Australia and New Zealand Clinical Trials Registry. Trial Identifier: ACTRN12619001594112
Protocol version {3}	24/03/2020, Version 2.0
Funding {4}	Metro South Health SERTA (Study, Education and Research Trust Account) grant.

## Introduction

### Background and rationale {6a}

In Australia, breast cancer is the most common cancer in females with an estimated 19,535 new cases annually [1]. With advances in early detection and cancer treatment, such as surgery, post-operative radiotherapy, and pre- or post-operative systemic therapies including cytotoxic chemo-, endocrine, and anti-HER2 antibody therapies, the 5-year relative survival rate for breast cancer is estimated at 91% [2, 3]. Consequently, in 2018, there were at least 200,000 breast cancer survivors living in Australia [4]. Despite good survival outcomes, breast cancer survivors require supportive care including prevention of cancer recurrence, surveillance for secondary or new primary cancer, and management of a range of long-term bio-psycho-social effects from their cancer diagnosis and treatment. In addition, many cancer survivors need management of comorbidities as they are 2.5 times more likely to develop mental and behavioural problems and almost 1.5 times more likely to develop musculoskeletal conditions, circulatory conditions, and endocrine system disorders compared with non-cancer patients [5]. These health concerns highlight the importance of a comprehensive, well-integrated, patient-centred model of care for people following completion of breast cancer treatment.

The current models of post-treatment care in Australia are mostly hospital-based and specialist-driven and focus on surveillance for disease recurrence, rather than the holistic care needs of cancer patients. This model of follow-up care limits the integration between specialist institutions and general practitioners (GPs), overloads the specialist system, and is unsustainable to meet the demands of the ever-growing population of cancer survivors. Specialist-based follow-up carries the burdens of travel and out-of-pocket costs such as those for parking. Those in non-metropolitan areas face more major disruptions to engage in specialist-based follow-up. Therefore, there is a strong case for an integrated, shared post-treatment follow-up care model for breast cancer survivors that involves both cancer specialists as well as care provided in the community by GPs. Such a shared-care model is consistent with Cancer Australia statements [6], the Optimal Care Pathway for Breast Cancer [7], and international guidelines [8]. In addition, the literature suggests that such a model is feasible, acceptable, safe, and more cost effective and patient-centred than current models used within Australia [9, 10].

Despite the promising evidence base, a shared follow-up care model in which specialists in the acute cancer care setting and GPs collaborate is not routinely implemented across Australia and many developed nations. Barriers to such shared care include the lack of a coordination between multiple providers, lack of patient and provider knowledge about the benefits of shared care and how to implement it, insufficient or delayed communication between cancer specialists and GPs, and lack of awareness of available support such as funding models, tools, and resources [11, 12]. These barriers could be overcome if a Specialist Cancer Nurse advises stakeholders (patient and GPs) of the benefits of shared-care, facilitates effective and timely care coordination, and acts as the conduit between the specialist cancer multidisciplinary team and the GPs at key transition time points, such as completion of definitive primary and adjuvant treatment [13].

### Objectives {7}

The objective of the study is to test the feasibility of a prospective, pragmatic randomised controlled trial (RCT) of the EMINENT intervention—a nurse-enabled, integrated, shared-care model involving cancer specialists and GPs for early breast cancer post-treatment follow-up.

### Trial design {8}

This phase II pilot RCT aims to assess the feasibility of a larger definitive clinical trial. Outcome data will be collected at four timepoints (or five if Booster Nurse Clinic is attended): (*t*_1_) baseline (at enrolment ± prior to Booster Nurse Clinic, if relevant), (*t*_2_) 3 months, (*t*_3_) 6 months, and (*t*_4_) 12 months.

## Methods: participants, interventions, and outcomes

### Study setting {9}

This study is conducted in a large, Australian metropolitan tertiary teaching hospital and general practices.

### Eligibility criteria {10}

The study population consists of patients with early-stage breast cancer (i.e. no-distant metastases) or ductal carcinoma in situ (DCIS). Patients will be eligible to participate from 2 weeks prior to completion of definitive treatment (surgery or adjuvant chemotherapy) and up to 18 months after completion of treatment. Patients meeting all of the following criteria are eligible for inclusion: diagnosis of curable, early breast cancer; receiving care at the Princess Alexandra Hospital; able to speak and read English; 18 years of age or older; ambulatory at the time of recruitment; Eastern Cooperative Oncology Group (ECOG) performance status 0 or 1; able to nominate a GP or GP clinic to be involved in their follow-up; and access to a telephone. Patients meeting any of the following criteria are excluded: presence of severe mental, cognitive, or physical conditions that would limit the patient’s ability to provide informed consent.

### Who will take informed consent? {26a}

Potential participants are identified by the research nurse or treating clinician during multidisciplinary team meetings. Participants are approached by their treating clinicians to gauge their interest in the study and gain verbal consent to being approached by the research team. Participants are then contacted by the research nurse, screened for eligibility, and provided with study information, and after a time of reflection (at least 24 h), they sign the consent form with the research nurse. Table 3 outlines the different phases of the study and data collection.

### Additional consent provisions for collection and use of participant data and biological specimens {26b}

Consent to access Medicare and Pharmaceutical Benefits Scheme (PBS) data on service use that qualifies under the Medicare Benefits Schedule (MBS) will be obtained, including relevant claims details (date of service, Medicare item number, and description) and costs details.

## Interventions

### Explanation for the choice of comparators {6b}

Survivorship care of breast cancer survivors following completion of treatment is an important issue, especially in light of improving survival rates [2]. The shared-care model between specialists and GPs focusses on the complex care needs of breast cancer survivors, rather than solely on disease recurrence, and may influence patient health outcomes and service outcomes [10].

### Intervention description {11a}

#### Arm 1

The control group will receive usual follow-up care supplemented with a survivorship booklet on *Living Well After Cancer* published by Cancer Council Australia [14]. The usual care follow-up arrangement is a specialist-led model as determined by the treating surgeon, medical oncologist, and radiation oncologist. This specialist-led follow-up care is not standardised and with follow-up activities and schedules depending on individual patient needs and the discretion of the treating clinicians.

#### Arm 2

EMINENT is a multi-faceted intervention that includes a pre-specified shared-care pathway for post-treatment follow-up. The design of the EMINENT intervention is informed by a number of Cancer Australia statements, the Optimal Care Pathway [15], the self-efficacy model [16, 17], the Capabilities for Supporting Prevention and Chronic Condition Self-Management framework [18], and our extensive pilot work including a systematic review [19] and observational studies [20–23]. Table 1 outlines the active ingredients of the EMINENT intervention.

**Table 1 Tab1:** Active ingredients of the EMINENT model of care intervention for patients allocated to receive the EMINENT intervention

Active ingredient	Personnel involved	Specific activities
**Nurse Clinic** (30–60 min) *Mode: face to face or telehealth*	Specialist Cancer Nurse^a^ and patient	• Treatment summary • Survivorship care planning • Collaborative planning for health goals • Post-treatment education
**Booster Nurse Clinic**^**b**^ (10–30 min) *Mode: face to face or telehealth*	Specialist Cancer Nurse^a^ and patient	• Survivorship care planning • Collaborative planning for health goals
**Pharmacist Consultation**^**c**^ (20 min) *Mode: face to face or telehealth*	Cancer Pharmacist and patient	• Medication reconciliation • Medication education
**Case conference with GP** (5–30 min) *Mode: teleconference*	Specialist Cancer Nurse^a^ and GP (± one more healthcare team member)	• Nurse presents treatment summary and survivorship care plan • Follow-up responsibilities of the GP negotiated • GP questions answered • Additional education and support provided to other healthcare team members (e.g. Practice Nurse)
**Shared follow-up care** *Mode: face to face or telehealth*	Cancer specialist, GP, and Specialist Cancer Nurse^a^ and patient	• Cancer specialist reviews patient, orders mammogram, and completes full physical examination every 6 months for 2 years post-diagnosis, then every 12 months up to 5 years post-diagnosis • GP reviews patient as per survivorship care plan at least every 12 months (e.g. for general health and comorbidity management, chronic disease management planning, psychosocial screening, management of cancer treatment toxicities and cancer-related symptoms, allied health referrals) • GP contacts nurse interventionist with any patient concerns

^a^Medical Oncology Clinical Nurse Consultant, Breast Care Nurse, or McGrath Breast Care Nurse

^b^Offered to patients who have delays in GP involvement greater than 3 months (up to 18 months)

^c^Offered to patients who have completed chemotherapy and/or are scheduled to receive aromatase inhibitor, or have completed surgery and radiotherapy

After enrolment, participants who have completed chemotherapy and radiotherapy or those who will receive aromatase inhibitor will participate in a 20-min telehealth cancer pharmacist consultation for medication reconciliation and education prior to Specialist Nurse consultation.

A 30–60-min consultation with a Specialist Cancer Nurse is then conducted to provide a treatment summary, the shared follow-up care appointment schedule, and survivorship patient education (including the survivorship booklet on *Living Well After Cancer* published by Cancer Council Australia [14]) and to co-develop a draft Survivorship Care Plan (SCP). The SCP includes up to three SMART (Specific, Measurable, Achievable, Realistic, and Timely) goals that are developed by the nurse and patient in partnership using motivational interviewing and self-efficacy techniques. Due to the recent COVID-19 pandemic, where there are delays of 3–18 months before GP involvement, a second ‘booster’ Specialist Cancer Nurse consultation is offered to patients to update the SCP. The treatment summary and draft SCP is provided to the GP.

Within 4 weeks of the Specialist Cancer Nurse consultation, a 5–30-min case conference between the Specialist Cancer Nurse and the patient’s nominated GP is completed to communicate the treatment summary and shared follow-up care schedule and to finalise the SCP and negotiate the GP’s role in facilitating the SCP goals. The GP may propose changes or express if they are not willing to take part in specific care activities outlined in the SCP. The finalised SCP is then filed in the patient’s medical records and provided to the patient and the GP.

The shared, follow-up care schedule consists of 6-monthly patient appointments with a cancer centre specialist and annual appointments with the GP for 2 years post-diagnosis. Following this, the schedule consists of alternating 6 monthly appointments with a cancer centre specialist and GP for up to 5 years post-diagnosis. At 5 years post-diagnosis, patients are discharged to the care of the GP, as per usual care. The GP appointments will focus on reviewing the SCP; promoting general health; primary prevention, screening, and management of comorbidities; psychosocial health; cancer treatment toxicities; cancer-related symptoms; chronic disease management planning; and allied health referrals. The GP has direct telephone access to the Specialist Cancer Nurse in case of concerns or escalation for acute care review. The cancer centre specialist appointments focus on surveillance activities such as physical examination and imaging (i.e. annual mammogram).

### Criteria for discontinuing or modifying allocated interventions {11b}

The presence of any of the following criteria constitutes cause for the withdrawal of the participant: altered mental capacity resulting in inability to provide continuing informed consent, notification from treating oncologist and/or GP that the participant is not deemed to have the capacity to consent, and recurrence or progressive disease or death.

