
### Plans to promote participant retention and complete follow-up {18b}

Participants who deviate from the protocol are not withdrawn from the trial. Participants who withdraw from the trial nominate the degree to which they withdraw (i.e. whether they withdraw from active data collection ± passive data collection such as MBS/PBS data).

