## Statistical methods

### Statistical methods for primary and secondary outcomes {20a}

Descriptive statistics will be used to report on feasibility and process-related elements (e.g. recruitment, intervention, retention rates) as well as clinical and resource outcomes. Preliminary effect size estimates for patient and resource use outcomes will be calculated following intention-to-treat principles using generalised linear mixed models. The distribution of the mixed models will be chosen as appropriate for the data, for example, a linear model for scale data or a Poisson for count data. Models will be adjusted for variables used in stratification of the randomisation process. Residuals of all models will be examined for statistical assumptions using descriptive statistics and plots.

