### Methods in analysis to handle protocol non-adherence and any statistical methods to handle missing data {20c}

Preliminary effect size estimates for patient and resource use outcomes will be calculated following intention-to-treat principles using generalised linear mixed models. Patterns of missing data will be examined using chi-square and *t* tests. Missing data for the outcomes will be accounted for by using mixed models allowing the use of each available case by computing maximum likelihood estimates.

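### Recurrence or progression is listed as a cause for withdrawing the participant, which ends outcome collection on a natural reading and sits poorly with intention-to-treat estimation

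*Protocol article*

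**What the plan says.** The heading of section {11b} concerns stopping or changing the allocated intervention. Its text acts on the person instead: "The presence of any of the following criteria constitutes cause for the withdrawal of the participant". The causes are loss of capacity to give continuing consent, notification by the oncologist or GP that the participant "is not deemed to have the capacity to consent, and recurrence or progressive disease or death".

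Section {18b} takes a different line for non-adherence: "Participants who deviate from the protocol are not withdrawn from the trial". It also lets participants who withdraw choose how far they do so, separating active data collection from passive collection such as MBS/PBS data. It does not say what happens to someone withdrawn by the rule in {11b}.

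Under {20a}, effect estimates "will be calculated following intention-to-treat principles using generalised linear mixed models". Section {20c} deals with missing outcomes "by using mixed models allowing the use of each available case by computing maximum likelihood estimates".

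The primary endpoint is FACT-B at baseline, 3, 6 and 12 months ({12}, Table 3). Section {14} sets 30 patients per arm and disclaims hypothesis testing, but names first estimates of effect size as one of the purposes.

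**The concern.** A patient whose cancer recurs can usually still consent, complete a questionnaire and have records extracted. Recurrence therefore differs from the other causes in {11b}, where loss of FACT-B data largely cannot be avoided. It is also plausibly tied to what the trial measures: quality of life, emergency presentations, hospital admissions, referrals back to acute care and resource use.

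If withdrawal ends collection, observation stops when the outcome is likely to change. An intention-to-treat comparison needs outcomes after such events as well as before them. Without them, the model fills the gap from recurrence-free experience, and the quantity estimated moves away from the effect in everyone randomised. An analysis plan cannot repair this later, because the questionnaires were never administered.

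**Working it through.** **Step 1: what is withdrawn.** The heading of {11b} points to the intervention and the sentence points to the participant. Two of the other causes are incapacity to consent and death, both of which end participation in the trial. Withdrawal from the trial is therefore the natural reading, though the section does not say from what the participant is withdrawn.

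**Step 2: what follows for data collection.**

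| Section | Content | After recurrence |
|---|---|---|
| {11b} | Withdraws the participant | Follow-up not mentioned |
| {18b} | Graded choice for those who withdraw themselves | Not clearly applicable to withdrawal by rule |
| {18a}, Table 3 | FACT-B to 12 months; hospital records; MBS/PBS data | No statement that collection continues |
| {20a}, {20c} | Intention to treat; maximum likelihood on available cases | No mention of recurrence or death |

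**Step 3: what the model does.** Suppose recurrence occurs between the 3- and 6-month visits. Baseline and 3-month scores (2 of 4) stay in the model, in the randomised arm. The 6- and 12-month scores are missing. Maximum likelihood in effect predicts them from the patient's own scores before the event and from patients still observed. That is valid only if, given those scores, the missing values behave like the observed ones (missing at random). A fall caused by a recurrence between visits appears in no score before the event, so the assumption is doubtful for these patients.

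**Step 4: size.** The article gives no alpha, power, standard deviation or recurrence rate. The only figure to reproduce is the total, 2 × 30 = 60, which agrees. The rest is for scale and rests on assumptions.

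*Chance of at least one event among 60,* 1 − (1 − p)^60, for an assumed 12-month rate p of recurrence or progression:

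| p | Expected events (60p) | P(at least one) |
|---|---|---|
| 1% | 0.6 | 45% |
| 2% | 1.2 | 70% |
| 3% | 1.8 | 84% |
| 5% | 3.0 | 95% |
| 10% | 6.0 | 99.8% |

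*Shift in one arm's mean at a visit.* If k of 30 patients are unobserved and would have scored D SD below the rest of their arm, the mean of those observed is too high by k × D / 30.

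| k | D = 0.5 | D = 1.0 | D = 1.5 |
|---|---|---|---|
| 1 | 0.017 | 0.033 | 0.050 |
| 2 | 0.033 | 0.067 | 0.100 |
| 3 | 0.050 | 0.100 | 0.150 |

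This is a complete-case shift, at the upper end. The mixed model recovers whatever part of D was already visible in earlier scores. With the same D in both arms, the between-arm difference moves only by (k₁ − k₂) × D / 30.

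*Comparison with precision.* With 30 per arm and unit SD, the SE of a difference is √(2/30) = 0.258 SD, and the 95% half-width is 1.96 × 0.258 = 0.506 SD. One event moves the estimate by at most 0.050 / 0.258 = 0.19 SE. Three events in one arm and none in the other, at D = 1.5, move it by 0.150 / 0.258 = 0.58 SE.

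**The case against.** The strongest reply is that {11b} never says data collection stops. It sits under a heading about the intervention, {18b} provides graded withdrawal, and a journal article may leave such detail to a fuller protocol. Part of this stands: the text does not establish that every data source ends, and hospital-record and MBS/PBS data may remain obtainable. It does not remove the point. The rule is stated, its natural reading ends participation, and nothing shown says that FACT-B continues.

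Four stronger readings are tempting, and the documents do not support them.

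- A reader might infer that patients with recurrence are removed from the analysis, in flat contradiction of intention to treat. No section excludes anyone. Data before the event are analysed as randomised, so the tension is with follow-up and with the quantity estimated. The sentence in {18b} on protocol deviators does not prove a contradiction either, because recurrence is not a deviation.
- A reader might infer that selection depends on arm. Usual care is specialist-led, and the intervention keeps specialist review every 6 months for 2 years after diagnosis, with mammography. Different detection within 12 months is possible but not shown.
- A reader might infer that the retention figure is lost. Section {20a} reports retention descriptively, and withdrawals for recurrence can be counted there.
- A reader might infer a bias serious enough to undermine the trial. The shifts above are small against the SE, rest on assumed inputs, and arise in a pilot without hypothesis testing.

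It can also be argued that ending participation when a patient leaves the curable population is a legitimate choice of scope. If that is intended, the article should say so and should not describe the estimates as intention-to-treat without qualification.

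**Conclusion.** The point holds as a should-fix improvement. As written, {11b} works against the follow-up that {20a} and {20c} rely on, because it makes later values missing through a rule triggered by an outcome-related event. The likely numerical effect here is small: 0.017 to 0.050 SD in one arm's mean per event, against an SE of about 0.26 SD for the difference, and less after credit for earlier scores and for events in the other arm. Those figures assume that the affected patients would have scored 0.5 to 1.5 SD below the rest. The conclusion also rests on reading {11b} as withdrawal from the trial. The reason to act is that uncollected data cannot be recovered, and that the article intends its results to inform a definitive trial, where the same rule could keep its bias while the SE shrinks.

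**What to change.** Reconcile {11b}, {18b}, {20a} and {20c} along these lines:

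1. In {11b}, distinguish discontinuing the allocated intervention from withdrawing from data collection.
2. Record recurrence or progression, with its date, as an event and not as a cause for ending data collection.
3. With continuing consent, collect the scheduled FACT-B, hospital-record and MBS/PBS data to 12 months, and analyse them as randomised.
4. Apply the graded withdrawal of {18b} to anyone who wishes to stop.
5. Report deaths separately, by arm, and do not treat scores after death as ordinary missing data.

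Whether the allocated care pathway continues after recurrence is a clinical matter and is left to the clinicians.

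The cost is a wording amendment through the route in {25}. The visits are already in Table 3, and consent for MBS/PBS data is already sought under {26b}. The downside is some respondent burden for a few patients at a difficult time, which the graded withdrawal option limits.
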